### 1.3. Secondary Outcomes

Secondary exploratory objectives include describing preliminary trajectories in maternal reflective functioning, maternal distress, perceived social support, maternal emotional bonding with the infant, and health-related quality of life in young children. These outcomes will be examined descriptively and exploratorily, with the aim of assessing the suitability and sensitivity of the selected measures for use in a future controlled trial, rather than testing intervention effectiveness.

By examining feasibility, acceptability, and preliminary clinical trajectories across different maternal risk conditions, this study will provide information on the practicality of delivering an exclusively online VFI-RF intervention during the postnatal period and on the suitability of the selected procedures and outcome measures for future randomized controlled trials (RCTs). In parallel, the study will explore potential barriers to implementation and to a subsequent larger-scale RCT, as well as determine what amendments and/or additional information may be required to optimize the design, delivery, and evaluation of the intervention in future trials. The practicality of implementing these changes will also be considered.

Overall, these findings will be used to determine whether a definitive main study is: (a) not feasible; (b) feasible pending modifications to the study protocol; or (c) feasible as originally designed.

### 1.4. Trial Design

This multicenter study is an open-label, single-arm feasibility study using a pre–post design with a nested qualitative evaluation. The VFI-RF will be delivered synchronously online by a trained clinician. Assessments will be conducted at three time points: baseline (T0; infant age ~3 months), post-intervention (T1; infant age ~8 months), and follow-up (T2; infant age ~12 months). Qualitative data will be collected through semi-structured interviews to further explore mothers’ experiences with the intervention and inform refinements for future research. The study protocol was drafted in accordance with the recommendations of the SPIRIT (Standard Protocol Items: Recommendations for Interventional Trials) statement. The corresponding checklist is available as Supplementary Materials.

## 2. Materials and Methods

### 2.1. Participants and Intervention

#### 2.1.1. Eligibility

The study will include mothers in the perinatal period who meet criteria for one of two at-risk groups: (1) mothers presenting clinically significant anxiety and/or depressive symptoms and (2) mothers who have given birth to a preterm infant, defined as birth before 37 weeks of gestation.

#### 2.1.2. Inclusion Criteria

The inclusion criteria for the general eligibility (applies to both groups) will be: (i) mothers in the perinatal/postnatal period aged ≥ 18 years; (ii) adequate knowledge of Italian; (iii) access to a digital device and a stable internet connection sufficient for online sessions and study assessments.

For Risk Group 1 (anxiety/depression), the inclusion criterion will be the presence of clinically significant anxiety and/or depressive symptoms, as identified through screening with the Edinburgh Postnatal Depression Scale (EPDS; cut-off score > 9) and the Generalized Anxiety Disorder 7-item scale (GAD-7; cut-off score ≥ 10). Accordingly, anxiety symptoms alone will qualify mothers for inclusion when the GAD-7 score is ≥ 10, even in the absence of clinically significant depressive symptoms.

For the Risk Group 2 (preterm birth) will be: (i) having given birth to a preterm infant, defined as gestational age < 37 weeks.

#### 2.1.3. Exclusion Criteria

The exclusion criteria will be: (i) severe cognitive impairment substantially limiting comprehension of study procedures or engagement in the intervention; (ii) acute psychiatric condition requiring immediate/intensive treatment (e.g., active psychosis or acute suicidality); (iii) neonatal medical instability or severe infant medical conditions that may interfere with participation or completion of assessments; (iv) current participation in other structured parenting interventions specifically focused on mentalization and/or video-feedback; (v) unable or unwilling to provide informed consent.

#### 2.1.4. Sample Size

Given the feasibility nature of the study, the planned sample size was selected to provide adequate information on recruitment, retention, intervention completion, assessment completion, acceptability, and study procedures. Although a minimum sample size of *N* = 28 was estimated, increasing to approximately *N* = 36 after allowing for 20% attrition, the planned sample size of 48 participants provides an additional margin to support the study’s feasibility objectives, e.g., [31,32].

#### 2.1.5. Recruitment

Potential participants for the VFI-RF study will be identified and recruited through participating Italian centers. Recruitment will be conducted through the following sources:(i)Mothers with moderate-to-high anxiety and/or depressive symptoms will be recruited through a network of local and regional counselling and socio-health services (e.g., the Department of Mental Health, ASL Roma 1, Lazio Region).(ii)Mothers of preterm infants will be recruited through the Neonatal Units and the Neonatal Intensive Care Units (NICUs) of Hospitals in the Abruzzo region(iii)Public advertisements, including online announcements, local media, and flyers/pamphlets distributed in relevant community and healthcare settings.

A member of the research team will contact the heads of service (e.g., principals/directors), case managers, and/or other relevant staff within the participating organizations to provide information about the study. If the organization agrees to collaborate, staff will be asked to share written study information with individuals whom they consider potentially eligible. Interested individuals will then be contacted by a member of the research team. Alternatively, those who prefer to be approached directly by the research team may complete a “consent to contact” form authorizing a member of the team to get in touch. At this stage, it will be explicitly clarified that individuals are providing consent only to be contacted by the research team to discuss the study, rather than consenting to participate in the study itself. To maximize reach and accessibility, the study will also be promoted via online channels, local media, and posters/leaflets distributed through collaborating organizations. Interested individuals will then be able to contact the research team voluntarily to obtain further information.

Recruitment has not yet begun; we plan to begin participant recruitment in April 2026 and to complete it by the end of 2027.

#### 2.1.6. Procedure

Mothers who meet the inclusion criteria and voluntarily consent to participate will be sent a link to complete the baseline survey. Eligible mothers will complete the baseline assessment (T0) when their infants are approximately 3 months of age. Baseline measures will include self-report questionnaires assessing sociodemographic information, maternal reflective functioning, psychological distress, parenting stress, perceived social support, and attachment style. Mothers will then be invited to attend a virtual appointment (within the same week) to review and discuss baseline findings. Prior to the online meeting, a clinician with psychodynamic training will review the mother’s responses. During the first session, the clinician will conduct a clinical interview to clarify any ambiguous findings and to establish an initial therapeutic engagement. The intervention procedures will be agreed in detail with each participant. Specifically, mothers will be instructed on how to use the platform, a schedule of sessions will be established, and clear guidance will be provided on how to record the video, where and how to upload/send it, and the sequence of everyday caregiving routines to be filmed. During the video-feedback sessions, selected moments of mother–infant interaction (e.g., feeding, diaper changing) previously recorded by mothers and submitted to the researcher will be reviewed and discussed jointly.

The privacy and confidentiality of all video recordings will be strictly protected. Mothers will receive an individualized secure link to a dedicated cloud-based storage system accessible only to the researcher. Uploaded videos will be stored using a pseudonymized alphanumeric participant code. The code will be generated using the first two letters of the participant’s first name, the first two letters of the participant’s surname, and the last two digits of the participant’s year of birth. No full names or other directly identifying information will be included in the video file names.

Following completion of T0, mothers will participate in a structured mentalization-based video-feedback program delivered synchronously online over a five-month period, comprising ten fortnightly sessions. During the intervention, mothers will be asked to record brief videos (approximately 5 min) of everyday caregiving interactions with their infant following standardized instructions. Recordings will be shared securely with the clinician and reviewed during online sessions, in which selected interaction sequences will be collaboratively explored to promote maternal reflective functioning and sensitivity (see Section 2.1.7).

Post-intervention assessment (T1) will be completed when infants are approximately 8 months of age, using the same procedures as at baseline. A follow-up assessment (T2) will be conducted when infants are approximately 12 months old to examine the maintenance of effects over time. At both time points, participant feedback will also be collected to explore mothers’ experiences of and satisfaction with the VFI-RF (see Figure 1).

All assessments and intervention sessions will be conducted remotely via secure digital platforms (e.g., Qualtrics, Zoom, Teams), in accordance with data protection and ethical requirements. Clinicians and research staff involved in data collection and observational coding will follow standardized protocols to ensure consistency and reliability across time points and study sites.

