## Abstract

The postnatal period involves significant emotional and relational shifts that can challenge early mother–infant interactions, particularly under conditions of psychosocial vulnerability (e.g., maternal anxiety/depression) or infant-related risk (e.g., preterm birth). Maternal mentalization, operationalized as Parental Reflective Functioning (PRF), is a key protective factor for sensitive caregiving and dyadic regulation. Objectives: This protocol describes a multicenter, open-label, single-arm feasibility study evaluating a brief, fully online, mentalization-based video-feedback intervention (VFI-RF). The study is designed to assess the feasibility and acceptability of the intervention, rather than its efficacy. We aim to recruit 48 mothers, 24 in each of two risk groups, through socio-health services and neonatal intensive care units. Risk Group 1 will include mothers with clinically significant depressive and/or anxiety symptoms, defined as EPDS > 9 and/or GAD-7 ≥ 10, whereas Risk Group 2 will include mothers of preterm infants, defined as infants born before 37 weeks of gestation. Methods: The intervention consists of 8 + 2 synchronous online sessions over approximately 5 months. Mothers record brief everyday caregiving interactions (~5 min) to review with a trained clinician, focusing on the infant’s internal states and reflective meaning-making. Assessments occur at baseline (T0, infant age ~3 months), post-intervention (T1, ~8 months), and follow-up (T2, ~12 months). Primary feasibility outcomes include recruitment/referral metrics, uptake, retention, assessment completion, missing data, and participant-reported acceptability. Secondary exploratory clinical outcomes include maternal PRF, symptoms, parenting stress, social support, and mother–infant attachment, evaluated via validated self-report questionnaires. Results: The study is designed to evaluate referral and recruitment patterns, intervention uptake, and participant retention, as well as the acceptability and suitability of study procedures and outcome measures for a future controlled trial. Preliminary trajectories of change in maternal reflective functioning and early relational indicators will be examined descriptively and exploratorily. Conclusions: Findings will inform the feasibility and refinement of a brief online mentalization-based video-feedback intervention to support at-risk mother–infant dyads during the first postnatal year. Trial registration: Registered on Open Science Framework, osf.io/6g9ja, date of registration 4th March 2026.

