### 1.1. Research Question

This feasibility study aims to determine whether a brief, stand-alone, synchronous online mentalization-based video-feedback intervention (VFI-RF) can be successfully delivered and evaluated among mothers experiencing postnatal risk conditions.

Specifically, the study will address the following research questions:Can eligible mothers be successfully identified, recruited, and retained across the study period?Are the assessment procedures, including questionnaire completion and follow-up assessments, feasible and acceptable to participants?Are the privacy, video-sharing, and data management procedures acceptable and implementable in a fully online format?Do participant-reported satisfaction and qualitative feedback support the acceptability of the VFI-RF intervention and study procedures?

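### The video code is built from the mother's name and birth year, so it can be recognised without a key and is not guaranteed unique (minor confidentiality and data-management correction)

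*Protocol article*

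**What the plan says.** The rule is in section 2.1.6 (Procedure) of the protocol article.

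- **Use of the code:** "Uploaded videos will be stored using a pseudonymized alphanumeric participant code".
- **Construction:** "The code will be generated using the first two letters of the participant’s first name, the first two letters of the participant’s surname". Two birth-year digits complete it.
- **Assurance on labels:** "No full names or other directly identifying information will be included in the video file names".
- **Access:** "Mothers will receive an individualized secure link to a dedicated cloud-based storage system accessible only to the researcher".

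Section 1.1 makes these procedures one of the four research questions: "Are the privacy, video-sharing, and data management procedures acceptable and implementable in a fully online format". The planned sample is in the Abstract: "We aim to recruit 48 mothers, 24 in each of two risk groups".

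The article does not say which identifier links the questionnaires at T0, T1 and T2.

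**The concern.** A pseudonym protects a participant when it cannot be traced to her without a separately held key. This code needs no key: name and birth year are enough to compute it. The people most likely to know both are close to the study, because section 2.1.5 has staff of collaborating services pass study information to mothers they think may be eligible. The files are recordings of routine care at home, and a recognised label also shows that the mother is in a study of postnatal risk groups.

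The second weakness is uniqueness. Two mothers whose names begin alike and who were born in the same year receive the same code, and the construction contains no random or serial element to separate them. Their videos would then carry one label.

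Both weaknesses lie in a procedure that the study itself sets out to evaluate. They come from a rule the article states, not from a detail it leaves to a fuller document.

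**Working it through.** **Identifiability.** No arithmetic is needed. The code has six characters: four letters of the mother's name and two digits of her birth year. Each comes from her personal data and none is random. The sentence about file names excludes full names and directly identifying information, which leaves partial names and birth year in place. The two statements can stand together, but the assurance does not cover what the code reveals.

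**Uniqueness.** The article gives no collision figure to reproduce, so the check is a birthday calculation.

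Inputs from the article:
- N = 48 mothers (Abstract), which gives 48 × 47 / 2 = 1,128 pairs.
- The three code components (section 2.1.6).
- Eligibility is limited to "mothers in the perinatal/postnatal period aged ≥ 18 years" (section 2.1.2), so far fewer than 100 birth years will occur.

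Inputs assumed, because the article gives none: the effective numbers of first-name beginnings (f), surname beginnings (s) and birth years (y). Effective means the number of equally likely categories that would give the same chance of a match. The components are treated as independent.

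Formulas: K = f × s × y; q = 1/K; expected number of matching pairs = 1,128 × q; P(at least one shared code) = 1 − ∏(1 − i·q) for i = 0 to 47.

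| f × s × y | K | Expected matching pairs | P(at least one shared code) |
|---|---|---|---|
| 676 × 676 × 100 | 45,697,600 | 0.00002 | 0.002% |
| 100 × 150 × 25 | 375,000 | 0.003 | 0.3% |
| 50 × 100 × 20 | 100,000 | 0.011 | 1.1% |
| 25 × 80 × 15 | 30,000 | 0.038 | 3.7% |
| 20 × 60 × 12 | 14,400 | 0.078 | 7.5% |
| 15 × 40 × 12 | 7,200 | 0.157 | 14.5% |

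The first row treats every letter pair (26 × 26 = 676) and all 100 two-digit years as equally likely. It is an unrealistic floor, because names and maternal birth years cluster. The other rows give the working range of about 0.3% to 15%. The probability is above zero in every row, but a duplicate is unlikely at this sample size.

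**Reach.** Section 1.2 counts retention and assessment completion from completed assessments and questionnaires, not from video files. A shared video label therefore does not enter those rates. Even if the same code did link the questionnaires, miscounting one mother would move an overall rate by 1/48 = 2.1 percentage points.

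**After the change.** With a serial number, or a random number drawn without repeats, the chance of a duplicate is 0 by construction. The label then holds no name letters or birth-year digits.

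**The case against.** The case for leaving the rule alone has real weight.

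- **Access is restricted.** Each mother has her own upload link, and storage is described as open only to the researcher. No access by referring services is described. This stands and lowers the practical risk. It does not settle the matter: section 2.1.6 also has recordings shared with the clinician, and Dosage and Administration has the clinician discuss the material within the research team. The article does not say who sees the labels.
- **The video shows the mother anyway.** For someone who opens the file, the code adds little. That is true, but a label can be read without opening the file.
- **A misfiled video would probably be noticed.** One psychologist delivers all sessions, and each video is viewed with the mother. This also stands, and it makes lasting harm from a shared code less likely.
- **A journal article is condensed.** Duplicate checks and custody of a key may sit in a fuller document, so their absence is not raised here. The construction rule itself is stated.

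Three stronger readings are tempting, and the article supports none of them. A reader might infer that retention, completion and missing-data rates or the mixed models of section 2.3 would be corrupted. That requires the video code to be the questionnaire identifier as well. The term participant code hints at this, but the article does not state it. A reader might also infer that a changed surname or a spelling variant would give one mother two codes across the waves. That requires the code to be regenerated or typed again at each wave, which is nowhere described. Finally, a reader might see a contradiction with the assurance about file names, but that sentence is not literally contradicted.

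**Conclusion.** The point holds as a minor confidentiality and data-management correction, with identifiability as its main part. That part rests on no assumption about name frequencies: the code follows from name and birth year, so it can be recognised without a key by anyone who has both and sees the label. The uniqueness part is secondary. The chance of any shared code among 48 mothers is roughly 0.3% to 15%, and this range depends wholly on the assumed effective counts and on treating the components as independent.

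The individual links and restricted access reduce the risk in practice. On what the article states, this point gives no reason to doubt the feasibility indicators or the exploratory models.

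**What to change.** In section 2.1.6, replace the construction rule with a study number that is random or sequential, is not derived from personal data, and is assigned by the team at enrolment. State that the key linking number to name is held separately from the videos and the survey data. Use the same number in each mother's individual upload link and survey link, which also settles how the assessment waves are linked.

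The change takes one or two sentences. The cost is a linkage list that the team must keep and protect. By section 2.1.5 recruitment had not begun, so on the article's account no stored file needs renaming. The change becomes more laborious once videos have been uploaded.

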#### 2.1.7. Description

##### Brief Online Mentalization-Based Video-Feedback Intervention (VFI-RF)

The intervention is a structured, brief, online VF program grounded in a psychodynamic and mentalization-based framework, specifically designed to enhance maternal reflective functioning within the mother–infant relationship. It comprises 8 + 2 sessions delivered synchronously over a 5-month period, spanning from when infants are approximately 3 months old to approximately 8 months of age.

The intervention will be delivered by a trained clinician within a psychodynamic framework. From this perspective, VFI conceptualizes the therapist as a mediator of meaning: through attuned reflection, emotional containment, and collaborative exploration, the clinician supports mothers in transforming implicit affective reactions into explicit, reflective understanding [33]. The therapeutic relationship therefore functions as a regulatory and interpretative scaffold, enabling mothers to develop more coherent representations of mother–infant interaction and to internalize more reflective ways of relating to their infant [34].

Phase 1. Initial Assessment and Therapeutic Engagement (Session 1). Session 1 will focus on clinical and relational assessment and on establishing the therapeutic frame. The study and intervention procedures will be introduced, the VF approach will be explained, and an initial therapeutic alliance will be fostered. This phase aims to create a secure, collaborative, and non-judgmental context, providing the foundation for subsequent reflective work. Clinicians and mothers also discuss the results of baseline assessment.

Phase 2. Video-Feedback Intervention Sessions (Sessions 2–9). The core of the intervention consists of VF sessions focused on everyday caregiving interactions. Mothers will be instructed to record brief videos (approximately 5 min) of routine interactions with their infant (i.e., free play, feeding, diaper changing, bathing) following standardized guidelines. Each session will typically include: (i) viewing the video sequence in its entirety; (ii) selecting and focusing on salient interactional moments, with attention to infant communicative cues and maternal responses; and (iii) clinician-guided reflective exploration, during which the clinician adopts a mentalizing stance and facilitates meaning-making. Across this phase, the clinician supports the mother in attending to and reflecting on her own emotional and mental states, recognizing the infant’s signals, needs, and intentions, and exploring moments of dyadic regulation as well as misattunement and repair. The emphasis is placed on fostering curiosity and reflective understanding rather than providing behavioral instruction. The intervention further conceptualizes the therapeutic relationship as an active mechanism of change, with the mother–clinician relational exchange supporting the development of mentalization and parental reflective functioning.

Phase 3. Final Restitution and Reflective Integration (Session 10). The final session will focus on reviewing the overall intervention process and reflecting on perceived changes in the mother–infant relationship. It will consolidate the reflective capacities developed across sessions and support the mother’s transition toward a more confident and reflective parenting stance. This phase aims to facilitate integration of the work completed during the program and to promote continuity of reflective caregiving beyond the intervention period.

Phase 4. Follow-up. Follow-up assessments will be conducted 12 months postpartum to examine the maintenance of intervention effects on clinical and psychological outcomes variables. In addition, qualitative data will be collected to explore mothers’ experiences of, and satisfaction with, the VFI-RF.

A visual description of the VFI-RF phases is provided in Figure 2.

